### 2.5. Outcomes

#### 2.5.1. Primary Outcome Measures

Primary outcome measure will be the incidence of PE from baseline during the pregnancy. PE is defined as diastolic pressure >90 mm Hg after two 4 h intervals or >110 mm Hg once; systolic pressure >140 mm Hg after two 4 h intervals or >160 mm Hg once, after 20 weeks of gestation in combination with proteinuria 2+ or more; >300 mg/24 h, >500 mg/L, or urinary protein/creatinine ratio >0.034 g/mmol.

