### 2.7. Sample Size

Reduction in PE will be considered the primary outcome variable, and an estimate of the mean difference in PE reduction will be used to calculate the sample size. The primary acceptance criterion will be the PE effect of the evaluated medical devices showing at least a moderate effect of 20%.

To show a reduction in PE from 20% to 12% (with alpha = 5%, beta = 80%), coefficient of intraclass correlation of 0.03 and in a unilateral proportion test, we initially calculated 440 subjects per group. Assuming a potential dropout rate of 10%, 880 participants were determined as the target for patient inclusion.

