#### 2.10.3. Statistical Methods

The final analysis of the data will be based on intention-to-treat and will be performed with the STATA MP 16.0 software (College Station, TX 77845, USA). All principal statistical analyses will be based on the clusters as allocated in the randomization [36]. Intention-to-treat analyses will be performed on the imputed data from all patients using multiple imputation by chained equations, based on a Monte Carlo–Markov chain algorithm under missing at random data hypothesis. Unilateral analysis to study the superiority of intervention over control group will be programmed. Data entry and preliminary checks for error and internal validity will be carried out at each study site, with corresponding statistical analyses conducted at a central level. A series of explanatory analyses will also be conducted in which clinics and/or individuals deviating from the protocol will be excluded. Additionally, per-protocol analysis using the same methodology as the intention-to-treat analyses will be performed based on participants with a complete set of outcome data at endpoint.

The main analytical technique used to assess the effect of intervention on the primary outcome will be an application of the Mantel–Haenszel test adapted to the cluster randomization design. Baseline tables will be created comparing the intervention groups with respect to both cluster-level and individual-level risk factors. 

Groups will be compared as at randomization. The primary endpoint will be estimated by the Kaplan–Meier method (survival analysis) and comparison of the different groups by the Log Rank test (*p* < 0.05). A multivariate analysis by a Cox regression model will be used to explore the relationship between the risk function associated with PE and the intervention after adjustment for site, amenorrhea at inclusion, gestational age, maternal age, and periodontal parameters at inclusion. Continuous outcome variables will be analyzed using mixed model regression, with the clinic status treated as a random effect. Analyses will also be conducted to explore the possibility of an interaction effect between intervention and clinic size. All statistical analyses performed will account for the within-clinic correlation that would invalidate the application of standard statistical methods. The results will be communicated according to CONSORT guidelines.

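### The primary endpoint is given two tests that are not clearly ranked, and the log-rank one has no named clustered form and does not match the incidence outcome

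*Protocol article*

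**What the plan says.** Section 2.5.1 defines the endpoint as an incidence: "Primary outcome measure will be the incidence of PE from baseline during the pregnancy". Section 2.7 sizes the trial on proportions, 20% against 12%, with a "coefficient of intraclass correlation of 0.03 and in a unilateral proportion test, we initially calculated 440 subjects per group".

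Section 2.10.3 then describes the analysis of this endpoint twice, in consecutive paragraphs:

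- "The main analytical technique used to assess the effect of intervention on the primary outcome will be an application of the Mantel–Haenszel test", in a form adapted to cluster randomization.
- "The primary endpoint will be estimated by the Kaplan–Meier method (survival analysis) and comparison of the different groups by the Log Rank test", with a threshold of p < 0.05.

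The second statement is not labelled secondary, supportive or sensitivity; secondary analyses are listed separately further down. The section declares one-sided testing for superiority in general, but the log-rank threshold is given without a side. The paragraph that holds the log-rank sentence also says: "All statistical analyses performed will account for the within-clinic correlation that would invalidate the application of standard statistical methods".

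The article does not say how delivery without PE enters the survival analysis. Section 2.6.4 says only that length of gestation and occurrence of PE will be taken from the records.

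**The concern.** Two tests of one endpoint, each presented as its analysis, leave open which result decides the trial. This matters most if the two behave differently under the null hypothesis. The Mantel–Haenszel test is expressly adapted to clusters, and the continuous outcomes get a clinic random effect. The log-rank test gets only the general promise. Its ordinary form assumes independent women, so it is one of the standard methods that the section itself says clustering would invalidate.

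The second issue is what is being estimated. PE during pregnancy can no longer occur once a woman has delivered. If Kaplan–Meier censors her at delivery, it estimates the risk that would apply if pregnancies did not end, not the proportion of women who develop PE. The outcome definition and the 20% and 12% planning rates refer to that proportion.

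**Working it through.** **Inputs from the article.** PE 20% against 12%, alpha 5% one-sided, ICC 0.03, 440 per group (2.7; the stated beta of 80% is read as power of 80%). There are 16 clinics with 55 women each (2.8), allocated 1:1 by clinic (2.1), hence 8 clinics per arm.

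**The plan's own figure.** The article states no type I error for either test; 440 per group is its only computed design figure.

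- Individually randomized, one-sided: n = [1.645·√(2·0.16·0.84) + 0.842·√(0.20·0.80 + 0.12·0.88)]² / 0.08² = 259 per arm.
- Design effect: 1 + (55 − 1)·0.03 = 2.62.
- Product: 259 × 2.62 = 679 per arm.

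So 440 is not reproduced. That is a separate matter, and nothing below depends on it. The exercise does confirm that the trial was sized as a comparison of proportions, not of event times.

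**Type I error if the log-rank test were unadjusted.** Clustering multiplies the variance of the test statistic by about the design effect (DE), so the one-sided error at nominal 5% is 1 − Φ(1.645/√DE).

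| ICC | DE at 55 per clinic | One-sided error |
|---|---|---|
| 0.005 | 1.27 | 7.2% |
| 0.01 | 1.54 | 9.3% |
| 0.03 (planned) | 2.62 | 15.5% |
| 0.05 | 3.70 | 19.6% |

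With 10% dropout (49.5 women per clinic) at an ICC of 0.03, DE = 2.455 and the error is 14.7%.

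**Check by simulation.** The model had 8 against 8 clinics of 55, beta-binomial PE risk, no treatment effect, delivery without PE censored, and 4,000 runs per setting. Timings had to be assumed: PE onset at 20 + 20·Beta(4, 1.5) weeks (mean about 34.5), and delivery without PE at a mean of about 38 weeks, limited to 24–42.

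- Ordinary log-rank, ICC 0.03: 16.2% at 20% PE and 15.1% at 16% PE.
- Ordinary log-rank, ICC near 0, same censoring: 5.3%. The excess therefore comes from clustering, not from censoring at delivery.

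**Does the missing ranking matter?** Two further simulations used the same clinics, an ICC of 0.03, 20% PE and assumed timings.

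| Log-rank version | Log-rank | Clinic-level test of proportions | Either significant |
|---|---|---|---|
| Ordinary | 15.0% | 4.9% | 15.0% |
| Clustered | 4.9% | 5.1% | 5.3% |

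With the ordinary test, the log-rank alone is significant in about 10% of null trials (15.0 − 4.9). With both tests clustered, the two nearly always agree.

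**Size of the Kaplan–Meier discrepancy.** Under the timings above, with delivery censored, 1 − KM averages 24.1% where the true cumulative incidence is 20.1%, and 19.3% where it is 16.0%. If women who deliver without PE are instead kept in the risk set to the end of the window, 1 − KM equals the crude proportion (0.2011 against 0.2011).

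**The case against.** The strongest reply is that the section already answers most of this. It calls Mantel–Haenszel the main technique, which ranks it first and agrees with the sample size. It bases the principal analyses on the clusters as allocated, and it promises within-clinic adjustment throughout. A journal article may leave the exact clustered log-rank test and the coding of delivery to the full protocol or analysis plan. Much of that stands, and it rules out several stronger readings that a reader might infer:

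- **That the plan ignores clustering and so has 15% type I error.** The log-rank paragraph itself says the opposite. The 15% belongs to an ordinary log-rank test, which the article does not say it will run.
- **That two tests by themselves destroy the 5% level.** With both clustered, allowing either to win gives 5.3%.
- **That the plan censors at delivery.** This is the usual coding, but the article does not state it. Kaplan–Meier does not force it either, as the last check shows.
- **That the Mantel–Haenszel test is itself anti-conservative with 8 clinics per arm.** That would require a normal reference distribution, and the article names none.

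The reply does not remove the conflict in the text. The word main gives only a partial ranking when the next paragraph assigns the primary endpoint its own estimator, test and threshold. The general promise is also not carried through to the named tests: later in the same section, t-tests, Mann–Whitney tests and ANOVA are listed with no adaptation. The mismatch between a survival estimate and an incidence outcome lies in what the article does state.

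**Conclusion.** The point holds as a conflict in the stated plan. One endpoint has two inferential analyses without a clear ranking, and the second has no named clustered form and does not correspond to the outcome definition or to the sample size.

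The consequence depends on what is run. A clustered log-rank test would have close to 5% one-sided error. An ordinary one would have about 15% at an ICC of 0.03 and 55 women per clinic, and about 9% at an ICC of 0.01. In the ordinary case, the trial's conclusion could depend on which sentence is followed.

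The overstatement of incidence (about 24% against 20%) requires censoring at delivery and rests on onset and delivery timings that are not in the article. It is an illustration of direction, not a prediction, and it concerns the estimate rather than the error rate.

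**What to change.** State one primary analysis: the one-sided, cluster-adjusted comparison of the proportion of women with PE by delivery. Use the Mantel–Haenszel test adapted to clusters and respect the stratification in section 2.9.1. Give it a small-sample reference. The degrees of freedom are the number of clinics less the arm and stratum parameters: 16 − 2 = 14 if unstratified, and 13 or fewer if stratified. A clinic-level permutation test within strata is an alternative.

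Label the time-to-PE analysis supportive and state its sidedness. Replace the plain log-rank test with a named clinic-clustered or clinic-permuted test. Replace Kaplan–Meier with a cumulative incidence estimate that treats delivery without PE as a competing event.

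The cost is wording in the protocol and analysis plan and a little programming. No new data are needed, because section 2.6.4 already collects length of gestation and occurrence of PE. The change should be made before any outcome data are seen by arm.

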## 1. Introduction

Pre-eclampsia (PE) remains a major source of maternal and perinatal morbidity and mortality, especially in low- and middle-income settings [1]. PE is a pregnancy-specific hypertensive disorder that is characterized by the development of placental endothelial dysfunction resulting in, among the most common diagnostic features, concomitant hypertension and proteinuria that may evolve into organs with fluctuating clinical specificities [2,3]. Obesity, chronic hypertension, metabolic or cardiovascular risks, and severe anemia, predisposing to endothelial dysfunction as part of an excessive systemic inflammatory response, have been found to be the highest risk factors of PE [4,5,6]. However, the prediction and prevention of PE is not possible, as the multifactorial pathogenesis of the different types of PE is not clearly identified [7]. The analysis of the alteration of placental microbiome is a possible therapeutic approach in the prevention and management of PE [8]. As an early signal of a future increase in cardiovascular and metabolic diseases, PE may warrant both educational and lifestyle interventions to improve perinatal outcomes [9,10].

In recent decades, numerous studies have shown that periodontal disease (PD) has contributed to prematurity and low birth weight [11,12,13]. PD is a chronic, multifactorial, non-communicable disease and inflammatory disease of polymicrobial origin resulting from an increase in pathobionts in the microbiota [14]. Maternal periodontopathogens may be linked to placental damage and premature pathogenesis [15], as well as the association between the presence of pathogenic oral bacteria in the placenta and adverse pregnancy outcomes [16]. PD may lead to systemic complications including pregnancy complications [17]. Current studies indicate that periodontal disorders during pregnancy, and particularly periodontal pathogens, may be related to the risk of PE [18]. Conversely, there is limited emerging evidence that pregnancy infers dysbiosis in the maternal oral microbiome [19].

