#### 2.6.2. Inclusion, Prenatal Examination, Oral Examination, and Baseline Interdental Microbiota Sampling (T1)

Participants will sign the informed consent form. A clinical obstetric and oral examination, followed by interdental microbiota sampling, will be performed for all participants.

Prenatal clinical examination

The obstetric clinical examination will include the measurement of weight, height, blood pressure, and the uterine height of the participants.

Biological analysis

The biological analysis will determine the level of red blood cells, white blood cells, neutrophils, C-reactive protein, creatinine, blood sugar, uremia, and proteinuria.

Oral clinical examination and sampling of the interdental microbiota

Two calibrated periodontists per site, properly trained before the beginning of the study, and who will be blinded regarding the group category at the time of the evaluation, will perform the periodontal assessment of all patients. Calibration of examiners will include a group of 32 experienced dentists. Intraclass correlation coefficients for PD and CAL will be calculated at the site level. The intra- and inter-examiner coefficients for CAL will range between 0.80 and 0.85, and between 0.75 and 0.85 for PD, respectively.

For all participants, the same four interdental sites (15–16, 25–26, 35–36, and 45–46) will be assessed; the interdental spaces between molars and premolars are the most susceptible to gingival inflammation [30,31]. The interdental diameter will be determined using a graduated conical probe—the CURAPROX IAP calibration probe (Curaden, Kriens, Switzerland) [32]. The working portion includes colored bands from the tip to the base corresponding to IDBs by increasing diameter. The largest section of each colored band corresponds to the cleaning efficiency diameter of the respective brush. This will make it possible to select the calibrated IDB (Curaden) appropriate to the diameter of the interdental space. Each previously selected tooth will be isolated using sterile cotton rolls, and the interdental biofilm will be removed using this sterile IDB. For each sample, the IDBs will be placed in 1.5 mL sterile microcentrifuge tubes and stored at 4 °C until further analysis.

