### 2.8. Recruitment

OP-PE trial will recruit 55 pregnant woman from each of the 16 clinical sites for a total of 880 subjects.

To identify participants, at the first visit for a pregnancy diagnosis, the physician will suggest that women who are less than 12 weeks pregnant, between the ages of 18 and 35, and who have never been pregnant before, participate in the study. If she responds positively, she will receive a trial information sheet and a consent form, and an inclusion visit will be scheduled by a qualified dental personnel. The total number of patients screened and recruited will be tracked. Patient volunteers will receive financial compensation.

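### The only covariate-adjusted analysis of pre-eclampsia, an exploratory Cox model, omits baseline blood pressure, body mass index and proteinuria, although all are measured at inclusion

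*Protocol article*

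**What the plan says.** Section 2.10.3 of the protocol article describes three analyses of PE:

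- The main technique is "an application of the Mantel–Haenszel test adapted to the cluster randomization design". No individual covariates are named.
- Kaplan–Meier estimation is planned with "comparison of the different groups by the Log Rank test". Again no covariates are named.
- "A multivariate analysis by a Cox regression model will be used to explore the relationship" between intervention and PE risk, "after adjustment for site, amenorrhea at inclusion, gestational age, maternal age, and periodontal parameters at inclusion". This is the only PE analysis with a covariate list. The list has no open-ended wording and does not defer to another document.

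Elsewhere the article shows which baseline predictors are available and which it considers important:

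- The Introduction gives as the leading PE risk factors "Obesity, chronic hypertension, metabolic or cardiovascular risks, and severe anemia, predisposing to endothelial dysfunction".
- Section 2.5.1 defines PE by blood pressure thresholds combined with proteinuria.
- Section 2.6.2 (T1) states "The obstetric clinical examination will include the measurement of weight, height, blood pressure, and the uterine height of the participants", and its biological panel includes "C-reactive protein, creatinine, blood sugar, uremia, and proteinuria". Table 1 confirms weight, blood pressure and proteinuria at T1. Height appears only in the text.
- Section 2.10.3 also plans baseline tables of individual and cluster-level risk factors by arm, but states no adjustment that follows from them.

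**The concern.** An adjusted analysis should contain the baseline variables expected to predict the outcome best. Here the outcome is built from blood pressure and proteinuria, and the protocol itself puts obesity and chronic hypertension at the head of the risk factors. Section 2.3.2 excludes neither condition, so this variation remains among the women enrolled. The list nevertheless uses two entries on what looks like the same quantity (amenorrhea at inclusion and gestational age) and none on blood pressure, body size or proteinuria.

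Only 16 clinics are randomised. A between-arm difference in these predictors is therefore quite possible by chance, and the one estimate a reader would turn to in that event would not correct for it. The baseline tables would show the difference and leave it there. Adding covariates after seeing those tables would look data-driven.

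**Working it through.** **Inputs from the article.** PE 20% versus 12%, one-sided 5%, intraclass correlation (ICC) 0.03, 440 per group (section 2.7); "55 pregnant woman from each of the 16 clinical sites for a total of 880 subjects" (section 2.8); 1:1 allocation by clinic (section 2.1), so 8 clinics of 55 per arm.

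**Assumed, because the article gives no figure.** The share of outcome variance explained by the omitted predictors (R²), their odds ratio per SD, and their own clinic ICC.

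**1. The plan's own figure.** For two proportions with pooled variance, one-sided 5% and 80% power:
- Without clustering: (1.645·√(2·0.16·0.84) + 0.842·√(0.16 + 0.1056))² / 0.08² = 259 per arm.
- Design effect: 1 + 54·0.03 = 2.62, so 259 × 2.62 = 679 per arm, and 679/0.9 = 755 after 10% dropout.

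The stated 440 does not follow from the stated inputs. That is a separate matter. It is used here only to fix the power from which any gain starts.

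**2. Power without and with adjustment.** Var(RD) = (0.20·0.80 + 0.12·0.88) × (1 − R²) × (0.97/440 + 0.03/8), and power = Φ(0.08/SE − 1.645). This lets the covariates remove the same share of variance within and between clinics, which is itself an assumption.

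| R² | SE | Power, normal | Power, t (14 df unadjusted, 13 df adjusted) |
|---|---|---|---|
| 0 | 0.0398 | 0.643 | 0.606 |
| 0.05 | 0.0388 | 0.662 | 0.622 |
| 0.10 | 0.0377 | 0.683 | 0.642 |
| 0.25 | 0.0344 | 0.751 | 0.710 |

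The gain is about 2 points at R² 0.05, about 4 at 0.10 and 10 to 11 at 0.25.

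**3. Which R² is plausible.** For a logistic model with a normal risk score and a mean risk of 16% (midway between 20% and 12%), R² on the risk scale is about 0.02, 0.06 and 0.10 at odds ratios of 1.5, 2.0 and 2.5 per SD. An R² of 0.25 needs an odds ratio of about 5 per SD. The rows at 0.05 and 0.10 are the ones to rely on.

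**4. Simulation.** 800 runs per scenario, 16 clinics of 55, outcome ICC about 0.03, cluster-level one-sided t-test with 14 df, without and with adjustment for one baseline score:

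| Odds ratio per SD | Covariate ICC | SE, unadjusted → adjusted | Power, unadjusted → adjusted |
|---|---|---|---|
| 1.5 | 0.01 | 0.0372 → 0.0372 | 0.67 → 0.67 |
| 2.0 | 0.05 | 0.0370 → 0.0351 | 0.67 → 0.70 |
| 2.0 | 0.10 | 0.0392 → 0.0355 | 0.62 → 0.70 |
| 2.5 | 0.10 | 0.0399 → 0.0343 | 0.61 → 0.72 |

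The gain runs from nil to about 12 points. The upper end needs a predictor that is both strong and clustered by clinic.

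**5. Chance imbalance.** SD of the between-arm difference in a standardised covariate = √(2(1 + 54·ICCx)/440).

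| Covariate ICC (assumed) | SD of difference | P(gap above 0.2 SD) |
|---|---|---|
| 0.01 | 0.084 | 2% |
| 0.03 | 0.109 | 7% |
| 0.05 | 0.130 | 12% |
| 0.10 | 0.171 | 24% |

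**6. What such a gap does.** At an odds ratio of 1.5 to 2 per SD, a 0.2 SD gap multiplies the odds by 1.5^0.2 = 1.08 to 2^0.2 = 1.15. In the other direction it divides them by the same factor, an 8% to 13% reduction that would turn a 20% risk into about 18% to 19%. The planned effect is an odds ratio of (0.12/0.88)/(0.20/0.80) = 0.55.

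**The case against.** The strongest objection is that the criticism falls on a secondary target. The Cox model is described as exploratory and the main test is the cluster-adapted Mantel–Haenszel test, so changing the covariate list leaves the primary result where it was. This stands.

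Three stronger readings are tempting, and the documents do not support them:

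- *That the primary comparison is biased or invalid.* Chance imbalance after randomisation is not bias in expectation, and a valid cluster-adapted test already allows for it in its error rate.
- *That about 10 points of power are lost.* This needs R² of 0.25, hence an odds ratio of about 5 per SD, and nothing in the article suggests that strength. A gain in the adjusted model would also not raise the power of the Mantel–Haenszel test.
- *That an imbalance could by itself create or hide the planned effect.* A shift in the odds of 8% to 13% is small beside an odds ratio of 0.55. It can move an estimate near the significance boundary, but it would not manufacture an effect of the planned size.

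Other counterpoints hold in part. Randomisation is stratified by site and clinic characteristics (section 2.9.1), clinics are chosen to serve similar populations, and women are nulliparous and aged 18 to 35 (section 2.3.1). These may limit imbalance, but none is tied to blood pressure or body size.

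The precision calculation is on the risk-difference scale. In a Cox model, omitting a prognostic covariate mainly pulls the conditional hazard ratio toward 1 and costs power.

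Proteinuria is not among the named risk factors. It qualifies as the baseline value of an outcome component. Severe anemia is named, and red blood cells are measured at T1, so the same reasoning would allow that variable too.

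Covariate choice is partly the analyst's judgement. This list, however, is fixed in the text and sits badly with the protocol's own account of risk, so it is not a detail left to a later plan.

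**Conclusion.** The point holds as a limited one. The only adjusted PE analysis omits baseline predictors that the protocol measures and that either make up the outcome or reflect risk factors it names. As written, the adjusted estimate does not correct for chance imbalance in them and forgoes some power. The likely power gain is about 2 to 4 points (assumed R² 0.05 to 0.10). It could be nil for weak predictors and reaches about 12 points only for strong ones clustered by clinic. The chance of a gap above 0.2 SD is about 7% at an assumed covariate ICC of 0.03, and 2% to 24% across 0.01 to 0.10. The omission itself is certain from the text. Its size rests on prognostic strengths and covariate ICCs that the documents do not give. The change is worth making because it costs almost nothing.

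**What to change.** Before unblinding, amend the adjusted PE model in section 2.10.3:

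- Add T1 systolic and diastolic pressure, body mass index from T1 weight and height, and T1 proteinuria.
- Keep maternal age and a single measure of gestational age at inclusion. Periodontal parameters may stay.
- Keep the randomisation stratification factors, and say what site means. It should enter as a stratum. The article also calls the 16 recruiting clinics sites, and an indicator for each clinic would be collinear with arm.
- Account for clustering with a clinic random effect (frailty) or a cluster-robust variance with a small-sample correction for 16 clinics.
- Report this estimate beside the cluster-adapted Mantel–Haenszel result, which remains the main analysis.

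The cost is wording only, since the values are already collected. At the planned rates about 440 × 0.20 + 440 × 0.12 = 141 PE events are expected before dropout, so four more covariates are not a burden. The downside is a slightly longer list and a conditional estimate that has to be explained.

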#### 2.6.3. Follow-Up Visits

Visits will be made according to the pregnant woman’s monthly follow-up schedule (Table 1). Obstetric clinical examination, biological analysis, and oral clinical examination will performed at each visit. Interdental sampling will be realized for all participants at 6 and 8 months of gestation. 

Participants in the intervention group will be asked about compliance with the study treatment (control of hygiene methods and techniques, and acceptance).

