Secondary analyses will also be performed comparing, as at randomization, the: (i) evolution of the pathogenic bacterial load of the interdental microbiota in the pregnant women intervention group compared to the control group, (ii) evolution of clinical signs of periodontal conditions in the pregnant women intervention group compared to the control group, and (iii) effect of individual oral prophylaxis during pregnancy on the risk of adverse perinatal outcomes. For dental clinical outcomes, mean and median values of clinical parameters for all oral, lingual/palatal, and proximal sites will be calculated per patient. Variations between the first and follow-up visits will be calculated.

Microbiological variables will be presented as total anaerobic counts, frequency of detection of target pathogens, counts of each pathogen studied, and proportions of each pathogen in the total microbiota. Total anaerobic counts will be log-transformed to match a normal distribution. 

The Shapiro–Wilk goodness-of-fit test and box plots will be used to determine the normal distribution of quantitative variables. Differences between groups at baseline and at follow-up visits will be determined by paired t-test or Mann–Whitney U tests for quantitative outcomes. In addition, clinical variables will be compared to repeated measures by ANOVA with Bonferroni post hoc correction controlling for visit for within-group comparisons, group (intervention or control) for between-group comparisons, and interaction between amenorrhea time and group. 

Results will be considered statistically significant at *p* < 0.05.

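### No analysis described for the repeated continuous secondary outcomes names both the clinic and the woman as a source of correlation

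*Protocol article*

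**What the plan says.** Section 2.10.3 (Statistical Methods) describes three routes for continuous outcomes.

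- **Mixed model.** "Continuous outcome variables will be analyzed using mixed model regression, with the clinic status treated as a random effect". No visit term, arm-by-visit term or woman-level term is mentioned.
- **Repeated-measures ANOVA** for the clinical variables, with Bonferroni correction. It includes visit, group and the "interaction between amenorrhea time and group". No clinic term is mentioned.
- **Paired t or Mann–Whitney tests** for group differences at baseline and at follow-up visits. No clinic term is mentioned.

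The same section also promises: "All statistical analyses performed will account for the within-clinic correlation that would invalidate the application of standard statistical methods".

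The data are repeated. Section 2.6.3 says "Obstetric clinical examination, biological analysis, and oral clinical examination will performed at each visit", which gives seven visits (T1 to T7), or eight if T0 in Table 1 is counted. Microbiota is sampled at T1 and then: "Interdental sampling will be realized for all participants at 6 and 8 months of gestation". At those three visits, "the same four interdental sites (15–16, 25–26, 35–36, and 45–46) will be assessed". For the dental clinical outcomes, "mean and median values of clinical parameters for all oral, lingual/palatal, and proximal sites will be calculated per patient". No corresponding step is given for the four microbiota samples. Section 2.5.2 defines the secondary outcomes as changes from baseline, and Section 2.10.3 says that variations between the first and follow-up visits will be calculated.

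**The concern.** The secondary question is how bacterial load and periodontal signs evolve in one arm compared with the other. The data have women within clinics and visits within women, so a valid SE for an arm-by-visit effect needs both levels. The described analyses split them: the mixed model names the clinic, the ANOVA handles repeated visits, and the visit-wise tests name neither. The last two also conflict with the section's own promise on within-clinic correlation.

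The same outcome could therefore be analysed in three ways with three different SEs, and the text does not say which one decides. The word 'status' after 'clinic' adds a small ambiguity, because it could be taken to mean the clinic's allocation, which cannot be a random effect.

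**Working it through.** The documents give no figure for the continuous outcomes, so there is nothing to reproduce. The check asks what each described analysis would report for the arm difference in change between two visits.

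**Inputs from the protocol:** 16 clinics of 55 women (Section 2.8), hence 8 clinics per arm at 1:1; ICC 0.03 (Section 2.7, given for pre-eclampsia only).

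**Assumptions:** total variance 1; ICC 0.03–0.05 for the continuous outcomes; within-woman correlation ρ = 0.3–0.7 after removing the clinic; the visit-specific share of the clinic variance is 0, one fifth or one half.

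**Notation:** s_cv = ICC × share; s_w = (1 − ICC)ρ; s_e = (1 − ICC)(1 − ρ). One value per woman per visit.

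**Variance of the arm contrast in change**

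- True: (2/8) × 2 × (s_cv + s_e/55)
- Reported with a clinic intercept only: (2/8) × 2 × (s_w + s_e + s_cv)/55
- Reported with a woman effect only (the ANOVA): (2/8) × 2 × (s_e + s_cv)/55

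The factor (2/8) × 2 cancels in the ratios.

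**Example:** ICC 0.05, share one half, ρ = 0.5. Then s_cv = 0.025 and s_w = s_e = 0.475.

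- True: 0.025 + 0.475/55 = 0.0336
- Clinic only: 0.975/55 = 0.0177; SE ratio √(0.0177/0.0336) = 0.73
- Woman only: 0.500/55 = 0.0091; SE ratio √(0.0091/0.0336) = 0.52

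**Range over ρ = 0.3–0.7 and ICC 0.03–0.05 (reported SE / true SE)**

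| Visit-specific share of clinic variance | Clinic intercept only | Woman effect only |
|---|---|---|
| 0 | 1.20–1.83 | 1.00 |
| one fifth | 0.89–1.25 | 0.59–0.82 |
| one half | 0.69–0.94 | 0.43–0.68 |

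Leaving out the woman effect alone makes the SE of change too large. Too small an SE requires clinic-by-visit variation. A woman intercept added without a clinic-by-visit term is therefore not a full repair.

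A simulation of the clinic-only model (1,500 trials per case) agrees. With ICC 0.05, share one half and ρ = 0.5, the SE ratio was 0.73 and the two-sided 5% test rejected 16% of the time. With ICC 0.03, no visit-specific share and ρ = 0.5, the ratio was 1.38 (formula 1/√0.5 = 1.41) and the test rejected 0.7%.

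**Visit-wise tests.** For an unpaired comparison of means at one visit that ignores clinic, the design effect is 1 + 54 × ICC, that is 2.62 at 0.03 and 3.70 at 0.05. The reported SE is then 1/√2.62 = 0.62 to 1/√3.70 = 0.52 of the true SE.

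**One change score per woman.** The woman effect cancels. Clinic-by-visit variance becomes between-clinic variance in change, which a clinic random effect absorbs, so neither error arises.

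**Microbiota sites.** Dental clinical parameters are reduced to one value per patient, so stacking of sites is an open question only for the four microbiota samples, taken at three visits.

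**The case against.** The strongest objection is that the mixed-model sentence describes no arm-by-visit analysis. It has no visit term and does not say that visits are stacked. The time-by-group interaction belongs to the ANOVA, which by design handles dependence within a woman. Outcomes defined as changes from baseline fit a model with one change score per woman, for which a clinic random effect is enough. Naming clinic as random does not say that it is the only random effect, and a condensed article may leave the full covariance structure to an analysis plan.

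Most of this stands. A reader might infer that the mixed model treats a woman's visits as independent, so that the SEs of every oral and microbial outcome are wrong. The text does not support that. Nor do the documents fix a direction or size: at a one-fifth visit-specific share the clinic-only ratio lies on both sides of 1, and the variance components are assumptions.

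The objection does not answer the conflict within Section 2.10.3. The ANOVA and the visit-wise tests are named without a clinic term beside a statement that all analyses allow for clinic. The ANOVA is given for clinical variables, while microbiological variables are described separately. The article states these methods itself, so this goes beyond detail left to another document.

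**Conclusion.** The point holds in limited form. Section 2.10.3 gives competing analyses for the repeated continuous secondary outcomes, and none names both clinic and woman. The ANOVA and the t or Mann–Whitney tests, as named, do not meet the section's own commitment on within-clinic correlation.

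The SE error in the mixed model is conditional on stacked visits, or stacked microbiota sites, entering with a clinic intercept alone. Its size and direction then depend on the assumed variance components, from 0.69 to 1.83 times the true SE over the range examined. The visit-wise tests understate the SE for any positive ICC. The ANOVA interaction does so only if clinic-by-visit variance exists. The primary outcome is not touched by this point. The change is worth making because it costs little and settles which analysis decides.

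**What to change.** Replace the ANOVA and the t or Mann–Whitney tests, for between-arm comparisons, with one mixed model of the follow-up values:

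- fixed effects for arm, visit, arm-by-visit and the baseline (T1) value, with T1 not also used as an outcome;
- random effects for clinic, clinic-by-visit and woman within clinic;
- small-sample degrees of freedom, because there are only 16 clinics.

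A simpler alternative is to model each woman's change at one named visit with clinic as a random effect.

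In either case, average the four microbiota sites per woman first, and write 'clinic' in place of 'clinic status'.

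The cost is a rewording of Section 2.10.3 and slightly more model code. No new data are needed.
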